### **8.2. Randomisation, blinding and treatment allocation**

This will be a single-centre randomized controlled trial. Randomization will be performed after intubation in the operation room by an electronic system, stratified for type of donor (living/ deceased). Since patients and physicians will notice post operatively the presence of an externalized stent, the study cannot be blinded.

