### 10.2. Secondary study parameter(s)

The following outcomes will be studied using a linear mixed model:

- The level of creatinin and eGFR after transplantation
- The answers to the SF-36 questionnaire
- The answers to the EuroQol questionnaire
- The answers to the work related questionnaire

As predictors we use indicator variables for the different time points and an interaction of each of the follow-up time points with the treatment arm. Note that at baseline we see both arms of the trial as a single group.

For each response we choose the most suitable covariance structure from the compound Symmetry, compound symmetry heteroskedastic autoregressive, autoregressive Heteroskedastic, Toeplitz and heteroskedastic Toeplitz based on the Akaike information criteria. Nonsignificant terms will not be removed from the model. The primary contrast we test is whether the profiles of the arms overlap. When the result of this multivariate test is significant we will also test the results at the various follow-up time points. Note that we will not apply a correction for multiple testing looking at multiple responses.

The following categorical outcomes will be compared between the treatment arms by means of a continuity corrected Chi square test:

- Hematuria
- Urinary tract infection
- Urosepsis
- Reoperation
- Radiologic interventions
- Tacrolimus toxicity
- Kidney replacement therapy
- Rejection
- Graft failure
- 

When any cell is empty or when more than 20% of the expected counts are less than five Fishers exact test will be performed for this outcome instead of the Chi square test.

The following continuous outcomes will be compared between the treatment arms by means of a Mann-Whitney U test:

- First and second warm ischemia time
- Cold ischemia time
- Time needed to make an urether-bladder anastomosis
- Blood loss during transplantation
- Duration of transplantation
- Duration of admission

All tests will be performed in a two-sided fashion with an alpha of 0.05. No multiplicity adjustment will be made. We will present the baseline characteristics of both treatment arms by showing the median and IQR for continuous variables and numbers and percentages for categorical variables. No statistical test will be performed on these values.

The cost effectiveness of the double J stent will be calculated as followed:

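### The closed list of covariance structures in Section 10.2 leaves out unstructured, so single-visit standard errors in the secondary mixed models can be wrong in either direction

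*Protocol*

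**What the plan says.** Protocol Section 10.2 applies a linear mixed model to SF-36, EuroQol, the work questionnaire and kidney function ("The level of creatinin and eGFR after transplantation").

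- **Mean model:** "As predictors we use indicator variables for the different time points and an interaction of each of the follow-up time points with the treatment arm". The baseline mean is shared: "Note that at baseline we see both arms of the trial as a single group".
- **Covariance:** "For each response we choose the most suitable covariance structure from the compound Symmetry, compound symmetry heteroskedastic autoregressive", continuing "autoregressive Heteroskedastic, Toeplitz and heteroskedastic Toeplitz based on the Akaike information criteria". A comma seems to be missing. I read six candidates: CS, AR and Toeplitz, each with equal or visit-specific variances. No reading of the sentence includes unstructured or a structure based on actual time.
- **Testing:** "The primary contrast we test is whether the profiles of the arms overlap". Single follow-up times are tested only if that joint test is significant.

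Table 1 in Section 8.3 places the questionnaires pre-operatively and at week 2, week 6 and month 6. It lists no creatinine or eGFR visits. Section 8.2 states that randomisation is "stratified for type of donor (living/ deceased"; donor type is not among the predictors in Section 10.2.

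**The concern.** AIC can only rank the structures it is offered. AR and Toeplitz count visits, not weeks, so the 2-week gap across the operation, the 4-week gap and the roughly 20-week gap to month 6 all receive the same adjacent-visit correlation. CS does not depend on spacing, but it makes all six correlations equal. No candidate lets the pre-operative value relate to follow-up differently from the way follow-up values relate to each other, unless the difference happens to fit a visit-count pattern.

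This matters more than usual here because the baseline mean is shared between arms. Baseline adjustment then works entirely through the modelled baseline-to-follow-up covariance, so a wrong correlation there changes both the estimate and its standard error. Section 8.5 also lets participants stop the questionnaires, and with incomplete data a likelihood analysis relies further on the covariance. At stake are the standard errors, intervals and tests at each visit for quality of life, health state, work and kidney function.

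**Working it through.** Section 10.2 gives no figure for these models, so there is none to reproduce. Inputs from the protocol: four visits (Table 1, month 6 taken as week 26), 150 patients per arm (Section 4.4), two-sided alpha 0.05 and a shared baseline mean (Section 10.2). The true covariances are **assumptions**.

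**1. Parameter count.** Unstructured: 4 × 5 / 2 = 10. Heterogeneous Toeplitz: 4 variances + 3 correlations = 7. Difference: 3.

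**2. Formula.** With complete data, the arm effect at visit t is d_t = D_t − b_t·D_0. D is the arm difference in means and b_t = s_0t / s_00 comes from the fitted covariance s. With true covariance S:

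- model variance ∝ s_tt − s_0t² / s_00
- true variance ∝ S_tt − 2·b_t·S_0t + b_t²·S_00

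The common factor 2/150 cancels in the ratio model SE / true SE. Per-visit type I error is 2[1 − Φ(1.96 × ratio)]. Each listed structure was fitted at its likelihood-closest value and the one with the best expected AIC was kept.

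**3. Worked case: correlation decaying in real time.** Assume unit variances and correlation 0.8 × 0.95^(weeks apart). Adjacent pairs then have 0.722, 0.652 and 0.287, which Toeplitz must merge into one value. AIC picks heterogeneous Toeplitz. It fits a pre-operative-to-week-6 correlation of 0.389 (true 0.588), with variances 0.860 (pre-operative) and 1.078 (week 6). At week 6:

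- b = 0.389 × √(1.078 / 0.860) = 0.4355
- model variance = 1.078 × (1 − 0.389²) = 0.915
- true variance = 1 − 2 × 0.4355 × 0.588 + 0.4355² = 0.678
- ratio = √(0.915 / 0.678) = 1.16; per-visit error 2.3%

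**4. All cases (large sample; week 2, week 6, month 6).**

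| Assumed truth | Model SE / true SE | Per-visit error, % | 3-df test, % |
|---|---|---|---|
| Heterogeneous CS | 1.00, 1.00, 1.00 | 5.0, 5.0, 5.0 | 5.0 |
| Decay 0.95 per week × 0.8 | 1.10, 1.16, 1.10 | 3.1, 2.3, 3.0 | 4.6 |
| Decay 0.90 per week, unscaled | 1.17, 1.23, 1.19 | 2.2, 1.6, 1.9 | 4.6 |
| Questionnaire-like (low pre-operative correlation) | 0.91, 0.96, 0.98 | 7.3, 6.0, 5.5 | 5.6 |
| Kidney-like (pre-transplant 0.05; later 0.65, 0.45, 0.80) | 0.84, 0.86, 0.89 | 9.8, 9.0, 8.0 | 7.6 |

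The kidney-like row borrows the Table 1 visits, which the protocol does not assign to creatinine or eGFR. Variants of it gave 7.4% to 8.2% for the 3-df test.

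**5. Would AIC have chosen unstructured?** Where no listed structure held, expected AIC favoured unstructured by about 27 points or more. Under heterogeneous CS (5 parameters) it is worse by 2 × (10 − 5) = 10 points, so AIC would rightly keep CS there.

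**6. Simulation.** REML, 500 trials per case, 20% missing at month 6. The Monte Carlo standard error of a 5% rate is √(0.05 × 0.95 / 500), about 1 percentage point.

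| Truth | AIC pick: SE ratio | 3-df, % | Unstructured: SE ratio | 3-df, % |
|---|---|---|---|---|
| Heterogeneous CS | 1.01, 1.07, 1.04 | 4.4 | 1.01, 1.07, 1.04 | 4.4 |
| Decay 0.95 × 0.8 | 1.07, 1.16, 1.09 | 4.2 | 0.97, 1.00, 1.01 | 5.8 |
| Questionnaire-like | 0.96, 0.97, 1.04 | 5.0 | 1.03, 1.01, 1.05 | 5.0 |

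Both fits use the same simulated data, so dividing one ratio by the other removes much of the simulation noise. Decay: 1.07/0.97 = 1.10, 1.16/1.00 = 1.16, 1.09/1.01 = 1.08. Questionnaire-like: 0.96/1.03 = 0.93, 0.97/1.01 = 0.96, 1.04/1.05 = 0.99. Both agree with step 4. The kidney-like case was not simulated.

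**The case against.** The strongest reply has four parts.

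- **The gate protects the tests.** Visits are tested only after a significant 3-df test. If the arms do not differ at any visit, the planned sequence cannot produce false positives more often than that test does, and it stays near 5% in the questionnaire-like and decay cases. This stands. A reader might take the per-visit rates above as the trial's false-positive rates; they are not, because they ignore the gate. The gate does not protect the standard errors and intervals reported at each visit, or the remaining visit tests once a real difference has opened it.
- **Error is conditional.** A reader might infer that the standard errors will be wrong, or that unequal spacing defeats every candidate. The protocol supports neither. CS does not use spacing, and if heterogeneous CS is true the AIC choice does as well as unstructured. Under decay the tests are conservative.
- **Kidney function.** A reader might assume that creatinine and eGFR share the four questionnaire visits. Table 1 does not say so, and the protocol does not say whether a pre-transplant value enters the model. The near-zero pre-transplant correlation is an assumption as well. The largest error rates rest on this case, so they are illustrative.
- **Donor type is a separate matter.** It concerns the mean model, and no size is claimed for its omission.

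That a statistical analysis plan may refine the model does not answer the point: the protocol itself fixes the list and the selection rule.

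**Conclusion.** The point holds as a risk to secondary results. The list omits the one structure that assumes nothing about visit spacing and that four visits in 300 patients easily support. If the true questionnaire correlations do not follow a CS or visit-count pattern, single-visit standard errors and intervals can be off: from about 10% too small (week 2, questionnaire-like case) to 15% or more too large (real-time decay). The gating 3-df test remains near 5% in those cases, and there is no error under heterogeneous CS. For creatinine and eGFR the joint test could reach about 7.5%, but only if a nearly uncorrelated pre-transplant value enters a model with visits like those assumed. All sizes depend on assumed covariances. The Fisher test of PCN placement and the sample size are not affected, and nothing here bears on the primary conclusion.

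**What to change.** In Section 10.2, replace the AIC search with a pre-specified unstructured covariance for the four-visit questionnaire outcomes. Use it also for creatinine and eGFR where the number of visits allows, and state their visit schedule and whether a pre-transplant value enters. Name one fallback in case the model does not converge, for example heterogeneous Toeplitz with empirical (robust) standard errors. Add donor type, the randomisation stratum, as a fixed effect.

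Cost: a change of wording and of model code. For four visits it adds three covariance parameters to the richest structure now listed, negligible with 300 patients; where heterogeneous CS was true, unstructured lost nothing in simulation (3-df error 4.4% for both). Donor type must already be recorded for randomisation, so no new data are needed.

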### 4.4. Sample size calculation

This study aims to show that a double J stent results in fewer PCN placements. Based on an two-sided alpha of 0.05, 149 patients are needed to have an 80% power to reject the null hypothesis of no effect when tested with Fisher's exact test when the double J stent in fact reduces the probability of PCN placement from 9% to 1.5% (3,5) To allow for a few non evaluable cases we randomize 150 patients per arm. (SAS Power and Sample Size 14.1)

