$$\frac{\text{Costs Double J stent} - \text{Costs Splint}}{\text{Percentage of PCN placements in Double J stent arm} - \text{Percentage of PCN placements in Splint arm}}$$

The costs of the double J stent will include the costs of the cystoscopy in the outpatient clinic for the removal of the double J stent.

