## 13. STRUCTURED RISK ANALYSIS

### 13.1. Potential issues of concern

Stent placement is a very known phenomena and is broadly used in both urological and surgical operations. In this study we hypothesize that double J stent placement is superior in minimizing the number of urological complications, as double J stents have a retrospectively reported incidence of 0-5.4% (6-8) and our data with externalized single J stents report an incidence of 9-20% (5, 12) urological complications. We have considered the potential risk of the additional risk of the cystoscopy but we have found these risks acceptable and therefore included the double J stent in this protocol. The stents are both CE approved and are widely used worldwide.

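### Section 10.2 makes one ratio over a small difference in PCN percentages the only cost-effectiveness result; at 150 per arm it is unstable, can be undefined, and its sign does not identify the finding

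*Protocol*

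**What the plan says.** Cost-effectiveness is a stated secondary aim in Protocol section 2 and is listed again in section 8.1.2. The calculation is in section 10.2, introduced by "The cost effectiveness of the double J stent will be calculated as followed". The numerator is the cost of the double J stent minus the cost of the splint. The denominator is the "Percentage of PCN placements in Double J stent arm" minus the same percentage in the splint arm. One sentence on costs follows: "The costs of the double J stent will include the costs of the cystoscopy in the outpatient clinic". No cost amounts are given, and no passage describes collecting costs patient by patient.

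The expected size of the denominator comes from section 4.4, where the double J stent "reduces the probability of PCN placement from 9% to 1.5" per cent, with 150 patients randomised per arm. Section 13.1 gives a wider picture of the double J results: "double J stents have a retrospectively reported incidence of 0-5.4" per cent, which refers to urological complications and not to PCN placement.

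**The concern.** The denominator is the difference between two small event counts. At the planned rates, about 13 or 14 patients in one arm and about 2 in the other would have a PCN, so a few events either way change the ratio several-fold. If the counts are equal, the ratio cannot be computed. If the true effect is smaller than planned, the observed order of the arms may reverse.

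The sign is a separate difficulty. The ratio is positive in the best case for the double J stent and also in the worst, so a reader given only the ratio cannot tell which occurred. The protocol makes either cost direction plausible: the double J stent adds a cystoscopy, while section 1 cites a retrospective study with a 2-day shorter stay.

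At stake is whether the trial can give a usable answer to a declared secondary question. The primary comparison is not affected.

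**Working it through.** **Inputs.** PCN rates of 9% and 1.5%, 150 per arm, two-sided alpha 0.05, 80% power and Fisher's exact test come from section 4.4. The alternative double J rates are 3.8% (section 1) and 5.4% (sections 1 and 13.1). Both are urological complication rates, used here as assumed PCN rates. Costs are assumed fixed, because the protocol gives no amounts; the ratio then scales as 1/(PCN difference).

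**The plan's own figure.** Enumerating both binomial distributions, the exact power of the two-sided Fisher test at 9% versus 1.5% is 79.8% with 149 per arm and 80.2% with 150. The stated sample size of 149 is reproduced within rounding.

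**Spread of the ratio if the plan is right.** Write d for the splint rate minus the double J rate, so that a benefit is positive.
- d = 0.09 − 0.015 = 0.075. Cost per PCN avoided = incremental cost / 0.075 = 13.3 times the incremental cost.
- Exact central 95% range of the observed difference: 4/150 to 19/150, or 2.67 to 12.67 points. The multiplier runs from 1/0.1267 = 7.9 to 1/0.0267 = 37.5. The fold range is 19/4 = 4.75.
- Wald check: SE = √(0.09×0.91/150 + 0.015×0.985/150) = 0.0254. The interval is 0.075 ± 1.96×0.0254 = 0.0252 to 0.1248, a 4.9-fold range.
- Newcombe interval for observed counts of 13/150 versus 2/150: 2.4 to 13.0 points, a 5.3-fold range.

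**How often the denominator is zero or reversed** (exact enumeration, 150 per arm):

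| Splint vs double J | Zero | Reversed | Total |
|---|---|---|---|
| 9% vs 1.5% (plan) | 0.08% | 0.05% | 0.1% |
| 9% vs 3.8% | 1.7% | 2.2% | 3.9% |
| 9% vs 5% | 3.6% | 6.8% | 10.4% |
| 9% vs 5.4% | 4.3% | 9.2% | 13.5% |
| 9% vs 9% | 8.1% | 46.0% | 54% |

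The 5% row is an interpolated assumption. It shows that the share reaches about 10% only when the true effect is roughly half the planned one (4 points against 7.5).

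**Sign of the ratio as written.** The denominator is double J minus splint, so the planned benefit makes it negative (1.5 − 9 = −7.5 points). 'Reversed' above means reversed relative to that planned direction.

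| Double J costs | Double J PCNs | Numerator | Denominator | Ratio |
|---|---|---|---|---|
| cheaper | fewer | − | − | + |
| costlier | more | + | + | + |
| costlier | fewer | + | − | − |
| cheaper | more | − | + | − |

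Each sign covers two opposite conclusions.

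**The case against.** The strongest reply is that a cost difference over an effect difference is the standard incremental cost-effectiveness ratio, for which Fieller and bootstrap intervals exist. A missing interval is a detail that a statistical or health-economic plan may supply, and section 10.2 does not exclude one. This stands: a reader might infer that the estimator is invalid or has no usable measure of uncertainty, and the protocol does not support that. What remains is that the protocol has already fixed the estimator. A later plan that follows it inherits a quantity that is undefined at equal counts and ambiguous in sign.

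A reader might also infer that the ratio will commonly fail. Under the planned effect it fails in only 0.1% of trials. Larger contrasts in the protocol's own text are safer still. At 20% versus 5% (section 13.2) the share is essentially zero and the 95% range of the difference is 8.0 to 22.7 points, about 2.8-fold. At 17.3% versus 5.4% (section 1) the share is about 0.05% and the range about 4.1-fold. These too are complication rates and not PCN rates, but they show that instability depends on the true effect.

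It is also fair that section 10.1 already requires PCN numbers and percentages per arm, so the PCN difference can be recovered. The cost difference has no such provision.

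Finally, it is tempting to show the ratio only when the interval for the PCN difference excludes zero. That would be selection on significance. At 9% versus 5.4% the true multiplier is 1/0.036 = 27.8. Among trials favouring double J whose Wald interval excludes zero, the mean multiplier is about 13.8, so the stent would look about twice as good value as it is.

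**Conclusion.** The point holds in a limited form. Section 10.2 makes one ratio the only cost-effectiveness result. With 150 per arm, that ratio varies about 4.75-fold from its denominator alone even when the planning assumption is exactly right. Failure through a zero or reversed difference is negligible under the plan, about 4% at a double J rate of 3.8%, 13.5% at 5.4%, and about 54% if both arms have 9%. The sign ambiguity does not depend on these rates.

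The figures assume fixed costs and treat complication rates as stand-ins for PCN rates. If costs are measured per patient, their sampling error adds to the uncertainty. If fixed unit costs are intended, the numerator has little sampling error and the denominator dominates. This is a change that should be made to a secondary analysis; the primary test and the sample size are untouched.

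**What to change.** Amend the cost-effectiveness part of section 10.2 as follows.

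- Report the cost difference and the PCN risk difference separately, each with a 95% confidence interval.
- Where patient-level costs are available, describe the joint uncertainty by bootstrapping patients within donor-type strata, the stratification factor in section 8.2. Otherwise use fixed unit costs with a stated sensitivity range.
- Present incremental net benefit over a range of values per PCN avoided. It is defined when the PCN difference is zero and has one direction of benefit.
- Show the ratio alongside these whatever the significance of the PCN difference. When that difference is zero or reversed, state the quadrant: cheaper or costlier, with fewer or more PCNs.

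The cost is a few lines of text and a little more analysis; no additional patients are needed. The headline cost figure becomes less definite. The bootstrap depends on patient-level costs, whose collection the protocol does not describe, so the amendment should say which kind of cost will be used.

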### **10.3. Other study parameters**

Not applicable

### **10.4. Interim analysis (if applicable)**

No interim analysis will be performed.

## **11. ETHICAL CONSIDERATIONS**

### **11.1. Regulation statement**

The study will be conducted according to the principles of the Declaration of Helsinki (59th WMA General Assembly, Seoul, October 2008) and in accordance with the Medical Research Involving Human Subjects Act (WMO).

### **11.2. Recruitment and consent**

The recruitment will start when a favourable opinion by the accredited METC has been given to conduct the study. During the surgical outpatient visit, patients receiving a kidney of a living donor will be informed and asked for their cooperation by the investigator. This will be different in patients receiving a graft of a deceased donor. Patients who are on the Dutch transplant waiting list for a deceased donor, will not receive the information about the study during their surgical outpatient visit as the average waiting time on the waiting list is currently 4 years. The study will probably be finished at time they will receive a kidney transplant. The timing of a deceased kidney transplant is always unexpected and very often during after-hours. Therefore these patients will be informed and asked for their cooperation pre-operatively by the operating surgeon. These patients have time to consider participation until 2 hours before the operation. Informed consent will be signed before the operation.

### **11.3. Objection by minors or incapacitated subjects (if applicable)**

Not applicable

### **11.4. Benefits and risks assessment, group relatedness**

There is no additional risk for the patient or the operation. Patients in one or the other group may have benefit, but only with this randomized controlled trial we can identify the beneficial operation. As literature is inconclusive to which stent to use, we do not know the benefits. A drawback for the double J stent is the additional cystoscopy which is needed for stent removal. There are a few minor complications associated with a cystoscopy such as urinary traction, haematuria or dysuria.

